### Blinding

In this study, numbers 1, 2, 3, and 4 will replace the four groups in the case report form (CRF) table. Subjects will unaware of whether they are in the treatment or sham stimulation groups. In addition, baseline and treatment phase assessments will be implemented by a researcher without knowledge of allocation. Unblinding will be performed at the end of the data analysis for this study.

### Patient public involvement

The public or patients will not be involved in the design of this protocol.

### Intervention

The combined, low-frequency, high-frequency, and control groups will receive microcirculation improvement, hypotensive medication, and conventional rehabilitation treatment, according to their disease characteristics. Based on the treatments, different rTMS stimulation protocols will be administered to the three treatment groups. This study will be conducted by two experienced and trained occupational therapists qualified for rTMS intervention. The other two evaluators will be unaware of the patient grouping. We will remind the participants of the consultation in advance to understand the change of the patient’s condition, treatment status, compliance, and complete the relevant follow-up records.

#### Conventional treatment

Pharmacological treatment: All groups of patients will receive the corresponding pharmacological treatment according to the characteristics of their disease, such as blood pressure control, blood glucose, blood lipids, nerve nutrition, and other pharmacological therapies.Conventional rehabilitation treatment: This refers to the guidelines for exercise rehabilitation given in the 2011 edition of the Chinese Stroke Rehabilitation Guidelines [22], which mainly include (a) good limb position and active and passive joint mobility training; (b) core muscle strength training, balance training, and walking training; (c) prevention and treatment of spasticity; and (d) training of manual refinement and daily living self-care ability. Occupational therapy and physical therapy will be administered for 40 min each, twice daily for 2 weeks over a total of 10 days.

#### rTMS treatment

A CCY-I magnetic field stimulator (Irid Medical Equipment New Technology Co., Ltd., Wuhan, China) with a circular coil of 125 mm diameter will be used once daily for 20 min.

The patient will be placed in a supine position, fully relaxed, with the head held still in a positioning cap. First, the motor evoked potential (MEP) monitoring module will be activated and then connected to the lead. The center of the circular coil will be aligned with a representative area of hand function in the cerebral cortex, such that the coil will be tangential to the skull surface at 45°. Subsequently, a single-pulse magnetic stimulation pattern will be used to observe the responsive movements of the affected fingers. If stimulation of the primary motor cortex (area M1) detects a minimum MEP with an amplitude ≥50 μV in the short thumb adductor muscle at least 5 times out of 10, this point will be the target of the stimulus and the stimulus strength will be the hemispheric resting motion threshold (RMT) (Fig. 3).

**Fig. 3 Fig3:**
[figure not shown]
Sketch of the rTMS stimulation protocol. **A** Schematic diagram for attaching electrodes. **B** Diagram of the coil stimulation site

#### Stimulation parameters

Low-frequency combined with high-frequency rTMS group (LF-HF-rTMS group): patients will first undergo low-frequency rTMS treatment on the unaffected side, M1 area, at 1 Hz, 90% RMT, continuous stimulation, 600 pulses for 10 min, then high-frequency rTMS treatment on the affected side, M1 area, at 10 Hz, 90% RMT, intermittent stimulation, 600 pulses for 10 minLow-frequency rTMS group: patients will receive stimulation to the M1 region of the contralateral hemisphere, at 1 Hz, 90% RMT, continuous stimulation, 1200 pulses. The affected side will then undergo a 10-Hz sham stimulus, for 20 minHigh-frequency rTMS group: patients will receive stimulation to the M1 area of the affected hemisphere, at 10 Hz, 90% RMT, intermittent stimulation, 1200 pulses. The unaffected side will then undergo a 1-Hz sham stimulus, for 20 minSham stimulation group: patients receive stimulation in both hemispheres under the same set of parameters as the combined group, with the coil at 90° and perpendicular to the scalp without power output, but sounds will be produced

All patients will be strictly treated according to the 2021 TMS operation guidelines [23], and the treatment course will be 2 weeks. Patients’ vital signs and adverse reactions will be closely monitored during treatment, and they will be discharged without discomfort at the termination of the treatment.

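### The low-frequency arm cannot fit the stated 20-minute session and the high-frequency arm's length is ambiguous, which weakens the participant-blinding claim

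*Protocol article*

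**What the plan says.** All places are in the protocol article.

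- **rTMS treatment** gives one session length without distinguishing arms: the stimulator "with a circular coil of 125 mm diameter will be used once daily for 20 min".
- **Stimulation parameters, combined arm:** the unaffected side comes first, "at 1 Hz, 90% RMT, continuous stimulation, 600 pulses for 10 min". The affected side follows, at 10 Hz, intermittent, also 600 pulses in 10 minutes.
- **Low-frequency arm:** at 1 Hz and 90% RMT, "continuous stimulation, 1200 pulses. The affected side will then undergo a 10-Hz sham stimulus". No duration is attached to the active part, and the entry closes with 20 minutes.
- **High-frequency arm:** "at 10 Hz, 90% RMT, intermittent stimulation, 1200 pulses", again with no duration and no inter-train interval. A 1 Hz sham on the unaffected side follows, and the entry closes with 20 minutes.
- **Sham arm:** "patients receive stimulation in both hemispheres under the same set of parameters as the combined group".
- **Blinding:** subjects are not to know "whether they are in the treatment or sham stimulation groups".

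**The concern.** A pulse count and a continuous rate together fix a duration. In the low-frequency arm that duration already equals the whole stated session, yet a second block is placed after it. An operator cannot follow both sections. Session length, active pulses or contralateral sham has to give way, and two therapists could resolve it differently.

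Two things are at stake. The first is what the low-frequency comparator actually received. The second is participant blinding. If the low-frequency session is visibly longer than the sham session, or has no second-side stimulation, a patient in that arm who knows the schedules can tell that it is not the sham arm. Patients come from one inpatient unit over a two-week stay (Recruitment), so comparing notes is possible. FMA-UE is a performance scale, so patient expectation can affect it even when the assessor is blinded.

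**Working it through.** **Inputs** (Stimulation parameters, unless noted): session 20 min (rTMS treatment); combined arm 600 pulses at 1 Hz, then 600 pulses at 10 Hz in 10 min; sham arm as combined; low-frequency arm 1200 continuous pulses at 1 Hz, then sham; high-frequency arm 1200 intermittent pulses at 10 Hz, then sham; 19 patients per arm, 76 in total (abstract); 10 interventions (Background).

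**Formula.** Continuous train: minutes = pulses / Hz / 60. The parts are added because the text makes them sequential.

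**Reproducing the 20 minutes.** Combined arm: 600 / 1 / 60 = 10 min, plus the stated 10 min, gives 20 min. The sham arm has the same parameters, so also 20 min. The figure reproduces for these two arms.

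**Low-frequency arm.** Active part: 1200 / 1 / 60 = 20 min.
- Closing figure read as the sham part: 20 + 20 = 40 min.
- Closing figure read as the whole session: 20 − 20 = 0 min left for the sham.

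Neither reading gives a 20-minute session that contains both parts.

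**High-frequency arm.** The active time is not stated, so it has to be assumed.
- Pulse-on time only: 1200 / 10 / 60 = 2 min. This is a floor, since intermittent delivery must take longer.
- At the combined arm's pace of 600 pulses per 10 min: 1200 / 60 per min = 20 min. The text does not apply this pace to the arm.
- Closing figure read as the sham part: 2 + 20 = 22 min to 20 + 20 = 40 min.
- Closing figure read as the whole session: 20 − 20 = 0 to 20 − 2 = 18 min left for the sham, so the arm may fit.

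| Arm | 20 min = sham part | 20 min = whole session |
|---|---|---|
| Combined | 20 min (10 min each side) | 20 min (10 min each side) |
| Sham | 20 min (10 min each side) | 20 min (10 min each side) |
| Low-frequency | 40 min | 20 min, 0 left for sham |
| High-frequency | 22 to 40 min | 20 min, 0 to 18 left for sham |

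Over 10 sessions the first reading gives 200 min (combined, sham), 400 min (low-frequency) and 220 to 400 min (high-frequency).

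**What a patient could infer**, assuming knowledge of all four schedules. Without any cue, P(sham) = 19/76 = 25%.
- A low-frequency patient sees a longer session or only one side treated: P(sham) = 0.
- If only that arm stands out, the others have P(sham) = 19/57 = 33%.
- If both unilateral arms stand out, a 20-minute session leaves combined or sham: P(sham) = 19/38 = 50%.

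Order can be seen too. As written, the high-frequency arm starts on the affected side, and the combined arm (hence the sham arm) starts on the unaffected side.

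**The case against.** The strongest case on the other side has four parts.

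1. *The high-frequency arm is not shown to conflict.* This stands. A reader might infer that both unilateral arms, 38 of 76 patients, run to 40 minutes. The documents do not support that: the 40 minutes borrows another arm's pace, and on the whole-session reading the arm can fit 20 minutes.
2. *The closing 20 minutes may describe the whole session, in which case length reveals nothing.* This stands for length. It does not rescue the low-frequency arm, which then has no time for its sham and would show one treated side against two in the combined and sham arms.
3. *The Blinding section promises masking only of treatment versus sham.* This stands. A reader might infer that session length reveals allocation, or that a stated blinding between active regimens fails. Length at most separates unilateral arms from the combined and sham pair. It cannot tell combined from sham, and no masking between active arms is claimed.
4. *The consequences are limited.* This stands in part. Evaluators are described as unaware of grouping, two of the three primary outcomes are MEP latency and serum BDNF, and any extra coil time is sham, beside conventional therapy sessions of 40 minutes each, twice daily. That patients compare sessions and interpret them is a possibility, not a documented fact. FMA-UE remains exposed to expectation, and it is the outcome on which the sample size rests.

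That this is an article rather than the full protocol is no answer, because the figures it does print conflict.

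**Conclusion.** The point holds as an internal contradiction in one arm and an ambiguity in another. For the low-frequency arm (19 of 76 patients), the two sections cannot both be followed: the session is 40 minutes, or its sham has 0 minutes, against 20 minutes with two coil placements in the combined and sham arms. For the high-frequency arm the length is undetermined: 22 to 40 minutes on one reading, possibly 20 on the other.

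The low-frequency result takes the printed pulse count, rate and continuous delivery as they stand. If the sponsor confirms different parameters, the difference may disappear. With the printed ones, either resolution leaves a visible cue that the patient is not in the sham arm, which undercuts the Blinding section for comparisons involving the low-frequency arm and, depending on its actual timing, the high-frequency arm. The cue does not distinguish combined from sham. Whether blinding was in fact weakened depends on what was delivered, which the document does not show.

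**What to change.** - Reconcile rTMS treatment with Stimulation parameters. For each arm, state the active and sham time per hemisphere, the order of sides and the total session time, as the sponsor intends them. Which pulse count or duration is right is for the sponsor to confirm.
- As far as the confirmed parameters allow, keep the visible sequence and the total session length alike across arms.
- Check the session logs for what patients already treated received. Trial status says that recruitment and interventions are under way, so a clarification reaches only later patients.
- If length or sequence differed by arm, report this and limit the participant-blinding claim for the affected comparisons.

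The cost is a protocol clarification, an instruction to the two treating therapists and a review of the logs. No extra patients are needed. If aligning the visible sequence would change how sessions are delivered during the trial, it should be made as a dated amendment, with patients treated before and after it identifiable in the data.

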### Primary outcomes

The Fugl-Meyer upper extremity score scale (FMA-UE) will be employed to evaluate the patient’s upper extremity motion capabilities. It contains elements such as reflex, coordination, stability assessment, and motor assessment of the shoulder to hand and is divided into nine items with a score of 0 points indicating the inability to complete a movement, one point indicating partial completion, and two points indicating successful completion, for a total score of 66. The one who has a smaller score is the one who has severe motor disability.Latency: MEP latency is the time between the onset of stimulus in the motor cortex and the appearance of action potentials in the contralateral target muscle [24]. A stimulus with an intensity of 90% RMT will be applied to the M1 area of the affected hemisphere, and the action-evoked potentials of the contralateral thumb abductor muscle will be recorded, taking three waveforms with good repeatability to record their latency values.Measuring serum biomarkers. Peripheral blood BDNF expression levels will be quantified using human BDNF-ELISA kits (manufactured by ABclonal, RK00074) [25]. Five milliliters of venous blood will be drawn, and the supernatant will then be centrifuged for 10 min at 3500 rpm at 4 °C (Centrifuge 5810 R, Eppendorf, Germany). The samples will be promptly anonymized and stored in a refrigerator at − 20 °C. Approximately 1 week after collection, the frozen samples will be transported to the laboratory to Ningxia Medical Uni’s laboratory and maintained at – 80 °C until analysis.

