**Methods:**

Seventy-six subjects will be randomly divided into combined, low-frequency, high-frequency, and control groups based on the proportion of 1:1:1:1, with 19 cases in each group. All groups will have conventional rehabilitation, on top of which the combined group will receive 1 Hz rTMS in the unaffected hemisphere and 10 Hz rTMS in the affected hemisphere. The low-frequency group will be administered 1 Hz rTMS in the unaffected hemisphere and sham stimulation in the contralateral hemisphere. The high-frequency group will be administered 10 Hz rTMS in the affected hemisphere and contralateral sham stimulation. The control group will receive bilateral sham stimulation. Assessments will be performed at baseline, after 2 weeks of treatment, and at post-treatment follow-up at week 6. The primary outcomes are FMA-UE (Fugl-Meyer assessment-upper extremity), latency, and serum BDNF levels. The secondary outcomes are the National Institute of Health Stroke Scale (NIHSS), Brunnstrom staging (BS), modified Ashworth scale (MAS), Modified Barthel Index (MBI), central motor conduction time (CMCT), precursor proteins of mature BDNF (proBDNF), and matrix metalloproteinase-9 (MMP-9) levels. Adverse events, such as headaches and seizures, will be recorded throughout the study.

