### Secondary outcomes

The National Institute of Health Stroke Scale (NIHSS) is used to evaluate the neurological function state of patients with stroke. This scale includes 11 items. The total score ranges from 0 to 42 points; and the higher the score, the more severe the nerve injury [26].The Brunnstrom staging (BS) scale for assessing movement function improvement in stroke patients. It is divided into stages I–VI; the greater the staging, the superior the restoration of function.Modified Ashworth scale (MAS) to evaluate variations in the patient’s muscle tone on a scale of 0, 1, 1 + , 2, 3, and 4 [27]; the higher the grade, the greater the muscle tone.The Modified Barthel Index (MBI) will be administered to the assessment of activities of daily living [28]. The total score is 100; a score ≤ 50 is classified as severe functional impairment, 50–75 as moderate functional impairment, 75–100 as mild functional impairment, and > 100 as no functional impairment.Central motor conduction time (CMCT) refers to the conduction time from the cerebral cortex to the alpha motor neurons in the anterior horn of the spinal cord. An intensity stimulus of 90% RMT will be applied to the patient’s seventh cervical spine (C7), and transmission time from C7 to the thumb short abductor muscle will be measured to calculate the difference between the transmission time from the scalp to the electrode piece and the transmission time from C7 to the electrode piece [29].Measuring serum biomarkers: the human MMP-9-ELISA kit (produced by ABclonal, China) will be used to quantify the level of MMP-9 expression in peripheral blood, and a human ProBDNF-ELISA kit (Biosensis, USA) will be used to detect the peripheral blood ProBDNF factor concentration [25]. The same protocol will be used to detect BDNF.

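### MEP latency, a primary outcome, is to be recorded at 90% of the strength that the protocol itself uses to define when an MEP is present

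*Protocol article*

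**What the plan says.** The abstract names three primary outcomes: "The primary outcomes are FMA-UE (Fugl-Meyer assessment-upper extremity), latency, and serum BDNF levels".

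The section on rTMS treatment sets the threshold. Single pulses are given over M1, and the target point and strength are fixed when the stimulus gives a "minimum MEP with an amplitude ≥50 μV in the short thumb adductor muscle at least 5 times out of 10". The strength at that point is taken as the hemispheric RMT.

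Under Primary outcomes, latency is the time from the cortical stimulus to "the appearance of action potentials in the contralateral target muscle". For its recording, "A stimulus with an intensity of 90% RMT will be applied to the M1 area of the affected hemisphere", with the response read from the thumb abductor, "taking three waveforms with good repeatability to record their latency values". The article gives no number of stimuli and no minimum amplitude for this recording.

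Under Secondary outcomes, CMCT is the scalp-to-muscle time minus the C7-to-muscle time. For the C7 part, "An intensity stimulus of 90% RMT will be applied to" the seventh cervical level, recorded from the short abductor of the thumb.

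The Study design section places neurophysiology at baseline and after 2 weeks. The Stimulation parameters section also uses 90% RMT, as the treatment setting.

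**The concern.** Latency exists only if a response is evoked. The protocol has one criterion for an evoked response, the one that defines RMT, and it records the outcome at a strength 10% below the level that meets it. The article offers nothing that would resolve this: no other recording intensity, no recording during voluntary contraction, and no rule for an absent MEP.

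At stake is whether one of three primary outcomes can be measured and reproduced as written. If some patients give no usable waveform, the latency comparison rests on those who do, and that is no longer the intention-to-treat comparison that the Data analysis section promises for 19 patients per arm. Latency also enters the planned correlations with FMA and the serum factors, and it supplies the scalp-to-muscle part of CMCT if that part is recorded in the same way.

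**Working it through.** **Inputs from the protocol article**
- RMT criterion: MEP of at least 50 μV in at least 5 of 10 stimuli (rTMS treatment).
- Recording strength for latency: 0.90 × RMT (Primary outcomes).
- Waveforms needed: 3 (Primary outcomes).
- Number of stimuli, amplitude floor for latency, and response probability at 90% RMT: not given.

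No stated figure in the protocol bears on this point, so there is none to reproduce first.

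**Step 1, from the definition alone.** Read RMT as the lowest strength that meets the 5-of-10 criterion. A weaker stimulus then meets it less often, so the probability p that a single stimulus at 90% RMT gives a criterion MEP is below 0.5. This is a statement about single stimuli at the 50 μV level. It needs no outside figure.

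**Step 2, from stimuli to patients.** This step needs assumptions. Let the response probability follow a cumulative normal curve with 50% at RMT and spread s, as a share of RMT. Then p = Φ(−0.10/s). The chance of at least three criterion MEPs in n independent stimuli is 1 − Σ(k = 0 to 2) C(n,k) p^k (1−p)^(n−k). The expected number of stimuli for three responses is 3/p. The values of s and n are assumptions.

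| s (assumed) | p at 90% RMT | at least 3 in 10 | at least 3 in 20 | 3/p |
|---|---|---|---|---|
| 5% | Φ(−2.00) = 0.023 | 0.1% | 1.0% | 132 |
| 7% | Φ(−1.43) = 0.077 | 3.6% | 19.4% | 39 |
| 10% | Φ(−1.00) = 0.159 | 20.3% | 63.6% | 19 |
| 15% | Φ(−0.67) = 0.253 | 48.2% | 91.3% | 12 |
| 20% | Φ(−0.50) = 0.309 | 64.0% | 97.0% | 10 |

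For comparison, at p = 0.5 the chance of at least three in 10 is 1 − (1 + 10 + 45)/1024 = 94.5%.

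The chance of at least three in 10 passes one half at p of about 0.26, which corresponds to a spread of about 15% of RMT. Below that spread most patients would lack three criterion MEPs in 10 stimuli; above it most would have them. With 20 stimuli the result is much more favourable except for the steepest curves.

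**Step 3, CMCT.** The scalp-to-muscle time shares the latency problem if it is recorded at the same strength. The C7 part differs: RMT is defined by stimulating M1, so a percentage of it says nothing, either way, about whether a C7 stimulus evokes a response.

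**Step 4, the muscle.** RMT is found "in the short thumb adductor muscle at least 5 times out of 10", whereas latency and CMCT are read from the abductor. As written, the threshold belongs to one muscle and the outcome to another.

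**The case against.** The strongest reply is that the text conflict is conceded but little follows from it. The article requires three repeatable waveforms and does not limit the number of stimuli. The 50 μV level belongs to the threshold search, not to the latency recording, so smaller repeatable responses could be used. The spread of the response curve is not in the document, and at 15% to 20% of RMT about 10 to 12 stimuli would be enough on average. In the rTMS treatment section the word minimum qualifies the MEP, not the strength, so taking RMT as a minimum strength is the conventional reading and not a literal one. The sample size rests on FMA-UE, so the powered comparison is untouched.

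All of this stands, and it limits what can be said about consequences. A reader might infer that latency is largely unobtainable; that depends on an assumed steep curve, few stimuli and an amplitude floor that the article does not set. A reader might also infer that values will be missing more often in severely affected patients. The document gives no basis for this: RMT is individual, and a patient with no measurable MEP would lack a latency at any intensity. That the 90% figure was carried over from the treatment setting is likewise a guess.

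The reply does not remove the inconsistency. A strength called a threshold is still the protocol's only criterion for an MEP being present, and the outcome is recorded below it without explanation.

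**Conclusion.** The recording rule for a primary outcome is internally inconsistent as written and should be corrected. The firm part is per stimulus: on the usual reading of threshold, fewer than half of single stimuli at 90% RMT would give an MEP of 50 μV or more. The per-patient consequence is open. Three or more such MEPs in 10 stimuli have a chance of about 0.1% to 64% for assumed spreads of 5% to 20% of RMT, compared with 94.5% at p = 0.5. These figures rest on a cumulative normal curve, a 50% response at RMT, independent stimuli and the 50 μV level. Relaxing the last, or giving more stimuli, raises them.

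CMCT is affected through its scalp-to-muscle part. One might extend the argument and call the C7 stimulus subthreshold, but a threshold defined at M1 cannot show that; it also cannot show that the C7 stimulus is sufficient. Nor does the document support suspending latency as a primary outcome: the fault lies in the wording of a procedure, and an amendment can repair it. The point concerns outcome measurement only and says nothing about the treatment intensity.

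**What to change.** - Reconcile the rTMS treatment, Primary outcomes and Secondary outcomes sections so that the latency recording intensity agrees with the protocol's own criterion for an MEP being present. The level is for the trial's neurophysiologist to set.
- State the basis for the C7 intensity in CMCT separately from the M1 threshold.
- Name one muscle for RMT and latency.
- Keep the same recording rule in all four arms, and at baseline and week 2 within each patient.
- Flag recordings already made at 90% RMT, and report the number of absent MEPs by arm.

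The change is a wording amendment and needs no extra visit or equipment. If practice already differs from the text, only the text has to change. The real cost is comparability. The Trial status section says the study began in June 2022 and was still under way at publication, so patients recorded at 90% RMT may not be comparable with later ones. The analysis must therefore note which recording rule each patient had.
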